### Missing Data

Baseline variables used by the AFC tool are routinely collected in the electronic health record and are therefore expected to be minimally missing. For follow-up outcomes, mortality is centrally collected (and therefore not expected to yield missing data). However, intercenter variability in data capture may occur. Therefore, for time-to-event outcomes (survival), patients will be censored at the last known follow-up in accordance with standard survival analysis methods. For binary and continuous secondary outcomes (eg, antimicrobial resistance and antibiotic use), we will assume data are missing at random and apply multilevel multiple imputation, using Rubin rules. For the window-based prescribing outcomes, windows without in-hospital systemic antibiotic exposure are considered not applicable (“no opportunity”) rather than missing and are excluded from the denominator of the cumulative primary end point. Patients without any applicable windows (no in-hospital antibiotic exposure in any assessment window up to day 100) will be excluded from the primary end point analysis, as the cumulative guideline-concordance proportion is not defined for these patients. The number and proportion of such patients will be reported by study phase. The proportion and patterns of missing data will be reported accordingly, and sensitivity analyses will be conducted using complete-case analyses and worst-case assumptions to assess the robustness of findings.

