### Sample Size Determination

The main aim of our study is to establish the assumed superiority of using the AFC over SOC in increasing the proportion of patients with first-line antibiotics prescribed. Therefore, we look at the proportion of patients receiving first-line or narrow-spectrum beta-lactam antibiotics within the total number of patients receiving antibiotics. The crossover design accounts for seasonal as well as intra- and interhospital differences in overall antibiotic use. Nevertheless, overall antibiotic use will be monitored at the participating sites during this trial’s period.

The following assumptions were applied.

For the control arm, in a recent retrospective study in UZ Leuven, involving 21,999 patients with pneumonia, pyelonephritis, infections associated with heart, kidney, liver, or lung transplantation; appendectomy; coronary artery bypass grafting; and total knee or hip replacement, we investigated the difference in antibiotic use between patients with and without BLAL [21]. It showed that 10.5% of patients with a BLAL received amoxicillin despite their label. Based on the latter, we estimate that 10% of the patients in the control group already receive first-line antibiotics. We add a 5% increase due to indirect learning of our protocol because we cannot exclude that treating physicians learn to use discordances in the medical file for delabeling or refinement of the allergy labels, independent of our study and AFC tool. Considering around 30% of hospitalized patients receive antibiotics during their stay [34], this brings the percentage down to 4.6% in the control group.

For the intervention arm, we previously showed that our CDS approach has the potential to delabel 38% of BLALs [30]. We add a margin of 5% for physicians or patients who refuse to delabel or be delabeled [9]. Considering around 30% of hospitalized patients will receive antibiotics during their stay, this results in an overall estimate for the intervention group of 9.9%.

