In case key assumptions differ importantly from those used in the initial calculations, we will implement a preplanned sensitivity and adaptation strategy focused on nuisance parameters rather than treatment effect estimates. Once the initial target number of inclusions has been reached, we will conduct a blinded (or arm-masked) internal review of (1) overall primary end point incidence, (2) observed within-period ICC and between-period correlation structure, and (3) completeness of follow-up and outcome ascertainment across centers and periods. In parallel, we will run sensitivity power analyses across plausible ranges of ICC or autocorrelation to quantify the robustness of power under departures from assumptions. If this review indicates that statistical power is likely to be compromised (eg, lower-than-expected event rate or higher-than-expected clustering), we will adapt by extending recruitment and/or adding additional crossover periods and/or centers, while keeping the intervention allocation scheme and primary outcome definition unchanged, depending on the available human resources to perform this. Any such modifications will be documented as protocol amendments and reflected in an updated statistical analysis plan. Importantly, to avoid operational recruitment gaps and preserve feasibility, recruitment will continue while this internal review is performed, and the adaptation decision will be based on updated nuisance-parameter estimates rather than interim efficacy signals.

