## Results

Recruitment for this multicenter crossover cluster-controlled study is ongoing across hospitals in Flanders, Belgium. Recruitment started in March 2025. As of March 2026, more than 3000 participants have been enrolled across 6 participating hospitals, which approximates the initially estimated sample size required for the planned power calculation.

According to the prespecified protocol, an interim assessment of nuisance parameters will be conducted in the following month to evaluate the initial design assumptions. Following this assessment, recruitment will continue with the participation of 3 additional hospitals, with data collection expected to continue until late 2026.

The final study database is anticipated to be locked in late 2026, after completion of follow-up. The prespecified statistical analyses will then be performed. The main study results are expected to be reported in 2027.

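### The sample size is set on all inpatients with a beta-lactam allergy label (4.6% vs 9.9%), but the primary analysis keeps only antibiotic recipients (about 15% vs 33% on the same inputs), so the planning figures do not describe the analysed end point or give its nuisance-parameter review a benchmark

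*Protocol article*

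**What the plan says.** Sample Size Determination first names the target quantity: "we look at the proportion of patients receiving first-line or narrow-spectrum beta-lactam antibiotics within the total number of patients receiving antibiotics". For control it starts from "we estimate that 10% of the patients in the control group already receive first-line antibiotics" and continues "We add a 5% increase due to indirect learning of our protocol". For intervention it takes a 38% delabeling potential with a 5% margin for refusal. Both arms are then multiplied by the 30% of inpatients who receive antibiotics. For control, "Considering around 30% of hospitalized patients receive antibiotics during their stay [34], this brings the percentage down to 4.6% in the control group"; for intervention, "this results in an overall estimate for the intervention group of 9.9" percent. The power statement treats 4.6% and 9.9% as the shares of patients with the primary end point, in connection with an expected 3285 inclusions.

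The analysed population is different. Missing Data states: "Patients without any applicable windows (no in-hospital antibiotic exposure in any assessment window up to day 100) will be excluded". This exclusion applies to the primary analysis, because the concordance proportion is undefined for them. Statistical Analysis repeats the exclusion.

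The adaptation paragraph of Sample Size Determination starts an internal review once the initial target number of inclusions is reached. It lists "a blinded (or arm-masked) internal review of (1) overall primary end point incidence" first, and gives a lower-than-expected event rate as an example of a reason to adapt. Results reports that "more than 3000 participants have been enrolled across 6 participating hospitals, which approximates the initially estimated sample size", with the review to follow in the next month.

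**The concern.** Multiplying by 30% moves the denominator from antibiotic recipients to all inpatients with a label. The exclusion rule moves it back for the analysis. The powered quantity is therefore not the analysed one, and the article prints neither the expected rates nor the expected number of patients for its own primary analysis.

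What is at stake is mainly the internal review. It is meant to detect a departure from the planning assumptions, but the only expected values available to it (4.6%, 9.9%, 3285 inclusions) belong to a different denominator from the end point. Progress is also counted in inclusions, of which only a part can contribute to the primary comparison.

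**Working it through.** **Inputs** (all from Sample Size Determination): control 10% plus 5 points; intervention 38% less 5 points; antibiotic share 30%; 3285 participants; within-period ICC 0.059; autocorrelation 0.6 with discrete time decay; two-sided 5%; stated power 80%.

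**1. Reproducing the printed rates.**
- Intervention: (0.38 − 0.05) × 0.30 = 0.099, exactly 9.9%.
- Control: (0.10 + 0.05) × 0.30 = 0.045; with the source figure of 10.5%, (0.105 + 0.05) × 0.30 = 0.0465. The printed 4.6% lies between the two.

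So the printed rates are proportions of all labelled inpatients.

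**2. The same inputs on the analysed scale.**
- Before the 30% factor: 15% vs 33% (0.046 / 0.30 = 15.3% if one works back from the printed control rate).
- Pooled incidence, equal arms: (0.15 + 0.33)/2 = 24%, against (0.046 + 0.099)/2 = 7.25%.
- Analysable patients: 0.30 × 3285 ≈ 986. The 30% describes antibiotic use during the stay, while the end point counts in-hospital exposure up to day 100. The true share is not given and could be higher.

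**3. Power on each scale.** Method: generalized least squares on cluster-period means, fixed period effects, the stated ICC and decay on both scales, binary variance averaged over arms, normal test. Figure 1 is not shown, so the number of hospitals and of repeats (cycles) of the four-period sequence is assumed, and the stated 80% cannot be uniquely confirmed or refuted.

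| Assumed layout | 4.6% vs 9.9%, N = 3285 | 15% vs 33%, N ≈ 986 |
|---|---|---|
| 6 hospitals, 3 cycles | 0.82 | 0.998 |
| 8 hospitals, 2 cycles | 0.815 | 0.998 |
| 9 hospitals, 2 cycles | 0.84 | 0.999 |
| 9 hospitals, 1 cycle | 0.55 | 0.97 |

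The 6-hospital entry depends slightly on how hospitals are divided among the sequences. For recipient shares from 20% to 60%, power for 15% vs 33% is at least 0.989 in the first three layouts. A small-sample t reference lowers all figures; the last layout then gives 0.91 on the recipient scale.

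**4. What the review would see if incidence is computed among recipients.**
- No effect (15% in both arms): pooled 15%, about twice 7.25%.
- 15% vs 20%: pooled (0.15 + 0.20)/2 = 17.5%, about 2.4 times 7.25%. Power with 986 recipients is only about 0.31 to 0.33 in the two- and three-cycle layouts.
- About 80% power with 986 recipients needs about 25% in the intervention arm in those layouts; pooled incidence would then be 20%.

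Against 7.25%, none of these looks lower than expected. Against 24%, all of them do.

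**The case against.** The strongest reply is that the mismatch errs on the safe side. On the plan's inputs, recipient-scale power is higher, and the article calls its calculation conservative. The first part stands, and it does not depend on the 38% delabeling input. With 9 hospitals, two cycles and a 30% share, 15% vs 20% gives 0.33 among recipients against 0.16 on the all-inpatient scale, and 15% vs 25% gives 0.82 against 0.45. A lower delabeling yield hurts both scales and is a separate question about effect size. The conservative label does not settle the matter, though: its stated ground is patient-level versus window-based scoring, not the change of denominator.

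Second, the adaptation paragraph does not fix the denominator of incidence. Events over all inclusions would compare directly with 4.6% to 9.9%, and event rate is only one example of why power might be compromised. This stands. It cannot be said that the review will use the wrong scale, only that its printed benchmarks do not match the end point as defined.

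Third, every input is printed, so 15% and 33% are one step away. The article also commits to reporting patients without applicable windows by phase, to monitoring antibiotic use, and to reviewing outcome ascertainment. That softens the omission, but none of it sets a target for analysable patients.

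A reader might also infer that the trial is underpowered, or that Results treats six hospitals as equivalent to nine and so loses power. The documents support neither. Power rises on the stated inputs. Results says only that the enrolled number approximates the initial estimate, and that recruitment continues with three more hospitals. Any six-versus-nine power comparison depends on the unseen Figure 1.

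**Conclusion.** The inconsistency is real and follows from the text alone: the powered rates and number describe all labelled inpatients, and the primary analysis describes antibiotic recipients. On the plan's inputs the analysed rates are about 15% vs 33%, pooled about 24%, in roughly 986 patients. That last number assumes the 30% in-stay share carries over to day 100. The mismatch does not show insufficient power; under the normal approximation, power is 0.97 or more in every layout tried, assuming the stated ICC also holds among recipients.

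The consequence is conditional. If the internal review computes incidence on the end point as defined and reads it against the printed rates, it could not recognise a shortfall such as 15% vs 20%, where power is only about 0.3 in the two- and three-cycle layouts assumed.

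**What to change.** Before the internal review is carried out:

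1. Restate the expected rates, pooled incidence, power and target number among patients with at least one applicable window, over a range of recipient shares (for example 20% to 60%), since the share up to day 100 is unknown. State the ICC assumed on that scale.
2. Name that denominator for the primary end point incidence examined in the review.
3. Add the number and fraction of analysable patients per hospital-period to the review's list, and express the target in analysable patients as well as inclusions.

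The cost is a wording change in the protocol and statistical analysis plan and a recalculation with the existing tool. No change to design, data collection or end point is needed. Timing matters: a benchmark reset after the pooled data have been seen is no longer prespecified.

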### Statistical Analysis

The primary endpoint is cumulative guideline-concordant use of first-line and/or narrow-spectrum beta-lactam antibiotics according to IGGI-based local guidelines, assessed across predefined assessment windows up to day 100 (days 1, 30, and 100). Within each window, guideline concordance is scored at the patient level in an any or ever manner as 1 if at least one in-hospital systemic antibiotic course is guideline-concordant and 0 if otherwise. If multiple courses occur within a window, the window is considered concordant if any course meets guideline criteria. This any or ever approach was chosen in line with the quality-improvement objective of the AFC intervention, capturing whether appropriate first-line therapy was achieved within a care window while limiting instability due to multiple within-episode treatment changes. Windows without in-hospital systemic antibiotic administration are considered not applicable (“no opportunity”) and are excluded from the denominator.

For each patient, a cumulative weighted guideline-concordance score is calculated at day 100 as the proportion of applicable windows with guideline-concordant therapy (*sᵢ/nᵢ*). The primary comparison between intervention (AFC) and control will use a binomial generalized linear mixed-effects model with logit link, modeling *sᵢ* out of *nᵢ*, including fixed effects for study phase and period, and a random intercept for hospital to account for clustering in the crossover design. A prespecified adjusted model will additionally include age, sex, and the Charlson comorbidity index. Patients without any applicable windows will be excluded from this analysis and reported separately. The primary estimand targets the period during which the AFC is expected to plausibly influence prescribing through contemporaneous decision support and short-term label adjustment.

Secondary endpoints include guideline-concordant beta-lactam use at each individual assessment window (including day 200), delabeling or refinement rate, beta-lactam tolerance, antibiotic switching, ICU admission, readmission, resistant organism outcomes, LOS, mortality, and cost outcomes. Outcomes at day 200 are analyzed as secondary durability measures, as longer-term prescribing may be influenced by label reappearance or documentation changes unrelated to the index intervention. Secondary endpoints will be analyzed using hierarchical mixed-effects models appropriate to outcome type (binary, continuous, or time-to-event), with fixed effects for study phase and period and clustering by hospital. Process evaluation outcomes will be analyzed descriptively.

Predefined subgroup analyses will assess potential effect modification by including phase-by-subgroup interaction terms in the primary model. Subgroups of interest are BLAL type (penicillin vs other labels), reported reaction severity category, time since label registration, infection type (prophylaxis vs therapeutic indication), ICU admission status, and hospital type (academic vs regional). Subgroup analyses will focus on the primary endpoint and are considered exploratory and hypothesis-generating. 

Moreover, because the AFC is expected to influence prescribing primarily through label delabeling or refinement, we will perform an exploratory implementation analysis within the AFC phase. Patients will be classified as with implementation if the BLAL was delabeled or refined after the AFC recommendation, and as not with implementation if otherwise. The cumulative primary endpoint (*sᵢ/nᵢ* up to day 100) will be summarized by implementation status; any between-group comparisons will be considered descriptive and interpreted cautiously, as implementation is a postallocation process measure and may be confounded.

No formal adjustment for multiplicity will be applied. Secondary and subgroup analyses will be interpreted with caution.

Sensitivity analyses will include evaluation of alternative covariance structures for within-cluster and within-period correlation (eg, exchangeable or autoregressive), with model selection guided by goodness-of-fit criteria, and estimation using generalized estimating equations with robust SEs to obtain marginal effect estimates and assess robustness to modeling assumptions. As a robustness check, we will report the proportion of patients with any recorded in-hospital follow-up within the shared EPR network (CWS) by study phase and period.

A detailed statistical analysis plan and data management plan will be finalized before database lock.

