**Methods:**

We are conducting a multicenter, open-label, crossover cluster-controlled study in 9 hospitals in Flanders, Belgium. All hospitalized adults with a BLAL are eligible, excluding patients in palliative care, discharged within 24 hours, or previously enrolled. Each hospital will alternate between intervention (use of the AFC) and control (standard practice) phases, separated by washout periods. The primary endpoint is cumulative guideline-concordant prescribing of first-line and/or narrow-spectrum beta-lactams following local antibiotic treatment guidelines, across predefined care windows up to day 100, expressed as a weighted per-patient proportion. Secondary endpoints include delabeling or refinement rate, beta-lactam tolerance, antibiotic switching, hospital length of stay, in-hospital and 3-month mortality, intensive care unit admission, readmission, multidrug-resistant organism colonization or infection, and costs. Based on prior data, we calculated that a total of 3285 participants are required to achieve 80% power to detect superiority of the intervention (4.6% vs 9.9% appropriate prescribing). Recruitment started in March 2025 and is ongoing.

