### Design

A multicenter, open-label, crossover cluster-controlled trial will be conducted to compare the use of our AFC on BLAL (intervention, I) and subsequent antibiotic prescription with current practice (control, C, ie, no AFC). All hospitalized adults with one or more BLAL will be included, except those previously enrolled in this study, discharged within 24 hours, or in palliative care. The primary endpoint is cumulative guideline-concordant prescribing of first-line and/or narrow-spectrum beta-lactams (based on the IGGI [Infectiologiegids/Guide d’Infectiologie] guidelines of the Belgian Society for Infectiology and Clinical Microbiology) across predefined care windows up to day 100, expressed as a weighted per-patient proportion. Within each predefined assessment window, prescribing is scored in an any or ever binary manner, and a cumulative weighted score per patient is calculated across applicable windows. Secondary endpoints include proportion of delabeled and refined BLALs; beta-lactam antibiotic tolerance; need to switch antibiotics; in-hospital and 3-month posthospitalization mortality; LOS; 3-month readmission rate; ICU admission rate; colonization and/or infection with methicillin-resistant *Staphylococcus aureus*, vancomycin-resistant *Enterococcus*, *Clostridium difficile* (*C. diff*); antibiotic and hospitalization cost, time, and resources needed for the AFC; and physician appraisal of the approach.

We chose a mono-faceted intervention without an awareness campaign or educational component (eg, e-learning for physicians on BLAL labeling and delabeling) to evaluate the impact of the AFC itself, enhancing its extrapolation afterward. To correct for interhospital variability, we choose a clustered crossover design. The crossover design also accounts for seasonal variability, for example, in overall antibiotic use.

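### The primary binomial model treats a patient's day 1, 30 and 100 windows as independent, so its standard error is too small if they correlate, and the unit of weight is left unclear.

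*Protocol article*

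**What the plan says.** All references are to the protocol article.

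- **Endpoint.** The Abstract describes guideline-concordant prescribing "across predefined care windows up to day 100, expressed as a weighted per-patient proportion". The Design section says that "a cumulative weighted score per patient is calculated across applicable windows". Statistical Analysis makes this concrete: "a cumulative weighted guideline-concordance score is calculated at day 100 as the proportion of applicable windows with guideline-concordant therapy", that is, s/n for each patient.
- **Windows.** There are at most three, at days 1, 30 and 100. Windows without in-hospital systemic antibiotics "are considered not applicable (“no opportunity”) and are excluded from the denominator", so n is 1, 2 or 3 among analysed patients.
- **Model.** "The primary comparison between intervention (AFC) and control will use a binomial generalized linear mixed-effects model with logit link", with s out of n as the response, "including fixed effects for study phase and period, and a random intercept for hospital to account for clustering in the crossover design". The adjusted version adds age, sex and the Charlson index. No patient effect, dispersion parameter or beta-binomial form is named.
- **Sensitivity analyses.** Other covariance structures are planned at cluster and period level, and generalized estimating equations (GEE) with robust standard errors.
- **One phase per patient.** Previous enrolment is an exclusion criterion.

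**The concern.** A binomial count of s out of n is valid only if the n windows of a patient are independent given the model terms. Without patient covariates the likelihood depends only on the hospital-period totals of s and n. Two windows from one patient then count exactly like two windows from two patients.

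Independence is hard to defend. The windows share the patient, the label and much of the clinical context. All of them fall in one phase, so the correlation adds fully to the variance of the phase contrast. The hospital intercept does not absorb it, because phase is compared within hospital. What is at stake is the error rate of the primary superiority test.

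There is also a question of target. The model gives a patient with three windows three times the weight of a patient with one. A per-patient proportion would ordinarily give them equal weight.

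**Working it through.** **The plan's own figure.** The plan gives no type I error or within-patient correlation to reproduce. Its 80% power (3285 participants, 4.6% vs 9.9%, ICC 0.059, autocorrelation 0.6) treats each patient as one binary outcome, so no such correlation enters. My generalized least squares calculation with 9 hospitals gives 54.8% power for one pass of the four-period sequences and 84.0% for two. Figure 1, which is not shown, is where the number of passes would be seen, so 80% can be neither confirmed nor refuted. Nothing below depends on it.

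**Inputs from the document.** n is 1 to 3; there are 9 hospitals; about 30% of patients receive antibiotics, so 0.30 × 3285 ≈ 985 are analysable; the test is two-sided at 5%.

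**Assumptions (not in the document).** The within-patient correlation rho, the mix of n, a hospital SD of 0.4 on the logit scale, and a control rate of 15.5% among treated patients (close to 4.6% / 0.30 = 15.3%). No hospital-by-period variance was included, so that the patient-level problem is isolated.

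**Formula.** Design effect DE = Σ n(1 + (n − 1)rho) / Σ n. The true standard error is √DE times the model's. Actual type I error = 2(1 − Φ(1.96/√DE)).

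Worked case, 50/35/15% with one/two/three windows:
- mean n = 0.50 + 0.70 + 0.45 = 1.65
- mean n(n − 1) = 0.35 × 2 + 0.15 × 6 = 1.60
- DE = 1 + rho × 1.60/1.65; at rho 0.5, DE = 1.485 and √DE = 1.219
- type I error = 2(1 − Φ(1.608)) = 10.8%

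| Mix (1/2/3 windows) | rho | √DE | Type I, formula | Type I, simulated plan model |
|---|---|---|---|---|
| 70/25/5 | 0.3 | 1.09 | 7.1% | 6.2% |
| | 0.5 | 1.14 | 8.5% | 8.8% |
| | 0.8 | 1.21 | 10.7% | 11.4% |
| 50/35/15 | 0.3 | 1.14 | 8.5% | 8.3% |
| | 0.5 | 1.22 | 10.8% | 10.4% |
| | 0.8 | 1.33 | 14.1% | 13.6% |
| 30/40/30 | 0.3 | 1.18 | 9.6% | 9.4% |
| | 0.5 | 1.28 | 12.7% | 13.8% |
| | 0.8 | 1.43 | 17.0% | 16.5%* |

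The simulations used 1000 null trials per row with beta-binomial patients. *This run of the mixed model did not finish; the figure is from 2500 trials with hospital as a fixed effect.

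**Controls.** At rho = 0 the plan's model gave 4.7% to 5.3%, so the excess comes from the ignored correlation. Patient-clustered standard errors, in the fixed-hospital version, gave 4.4% to 5.9% in every scenario.

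**The planned GEE.** With an independence working correlation, clustering on hospital and no small-sample correction (all assumed), it gave 15% to 18%, including at rho = 0. Nine clusters are too few for the uncorrected version.

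**Weighting.** In the 50/35/15 mix, the 15% of patients with three windows carry 0.45/1.65 = 27% of the weight. For illustration, let the control rate be 15.5% throughout and the intervention rate 25/33/41% for n = 1/2/3. The per-patient difference is 0.50 × 9.5 + 0.35 × 17.5 + 0.15 × 25.5 = 14.7 points. The window-weighted difference is (0.50 × 9.5 + 0.70 × 17.5 + 0.45 × 25.5)/1.65 = 17.3 points.

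**The case against.** **The size is unknown.** This stands. Neither rho nor the mix is documented. The day 100 window needs in-hospital antibiotics during a long stay or a readmission, so three-window patients may be few. The direction is secure for any positive correlation; the magnitude is conditional.

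**A hospital-by-period term would absorb part of it.** This stands in part. In a simulation with a 40/40/20 mix and rho 0.6 (400 runs, Monte Carlo error about 1.5 points), adding that intercept lowered type I error from 10.5% to 7.3% for one pass and from 14.5% to 9.5% for two. The same test gave 5.5% to 6.5% at rho = 0. The plan has no such term, and some inflation remains with it. Its absence is a separate issue, and its effect is not counted here.

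**The GEE with robust standard errors covers it.** Clustering on hospital would in principle absorb within-patient correlation. But it is a sensitivity analysis only, and on nine clusters it is not dependable without a small-sample correction.

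**Stronger readings.** A reader might infer that the model replaces the announced endpoint with a different one. The text does not establish this: it says 'weighted' without defining the weights, and it openly models s out of n, so window weighting may be intended. The two targets differ only if concordance or the effect varies with n. A reader might also infer that a course running across two windows is scored twice. That is plausible, but the document does not say how such a course is assigned.

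**Conclusion.** The point holds. The stated primary model leaves no room for correlation between a patient's windows, and any positive correlation makes the primary test anti-conservative. Over rho 0.3 to 0.8 and the three assumed mixes, the true standard error is 1.09 to 1.43 times the model's, and type I error is roughly 6% to 17% against a nominal 5%. Those figures rest on the assumed correlation and mix, and on leaving out hospital-by-period variance. They are not estimates for this trial, and the inflation is zero if all patients have one window or rho is zero.

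On weighting the conclusion is narrower: the model weights patients by n, the endpoint's weights are undefined, and the intended unit is ambiguous. That is a definition to settle, not a demonstrated bias.

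**What to change.** State whether windows or patients carry equal weight, and make the primary analysis allow for patient-level correlation accordingly:

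- **If window weighting is intended:** replace the binomial with a beta-binomial (overdispersed) model. It still gives more weight to patients with more windows, though less than in proportion to n, so it does not deliver equal patient weight.
- **If equal patient weight is intended:** analyse each patient's s/n with weight 1, summarised at hospital-period level.

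Report the other version as sensitivity. A patient random intercept is a less attractive route: it is weakly identified with one to three windows and turns the odds ratio into a patient-conditional one.

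The masked review of nuisance parameters described under Sample Size Determination could also report the within-patient correlation and the distribution of n, pooled over phases. That would replace the assumptions above with data before the analysis plan is finalised.

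The cost is a change of model wording, a sentence defining the weights, and a wider interval.
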